## 6. Schedule

|                                | One week before | Week 0 | Week 4 | Week 8 | Week 12 | Result report |
|--------------------------------|-----------------|--------|--------|--------|---------|---------------|
| Explanation and consent        | ⊙               |        |        |        |         |               |
| Urine equol test               |                 | ○      |        |        |         | ⊙             |
| Intestinal flora test          |                 | ○      |        |        |         | ⊙             |
| Dietary questionnaire          |                 | ○      |        |        |         | ⊙             |
| Blood test                     |                 | ○      |        |        | ○       | ⊙             |
| baPWV                          |                 | ○      |        |        | ○       | ⊙             |
| Body weight measurement        |                 | ○      |        |        | ○       |               |
| Visceral fat scan              |                 | ○      |        |        | ○       | ⊙             |
| AGE reader                     |                 | ○      |        |        | ○       | ⊙             |
| Supplement                     |                 | ←————→ |        |        |         |               |
| Climacteric symptom assessment |                 | ○      | ○      | ○      | ○       |               |
| Safety monitoring              |                 | ○      | ○      | ○      | ○       |               |

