## **Outline of clinical trial on equol and lactobionic acid supplement**

### **1. Research Objective and Background**

Equol is an active metabolite in which daidzein, a type of soy isoflavone, is metabolized by intestinal bacteria. Its structure is similar to that of the female hormone estrogen, and it has an estrogen-like action, which alleviates menopausal symptoms. , Suppression of bone loss, improvement of lipid metabolism and arteriosclerosis, etc. have been reported, and are expected to be effective for a wide range of women's health care.

On the other hand, the number of people who can produce equol in the body is as small as about 50% in Japan, and it is said that the eating habits, living environment, and intestinal bacteria, which are equol-producing bacteria, are involved in the equol-producing ability.

In this clinical study, it is considered meaningful to investigate and clarify the relationship between dietary habits and the types of intestinal bacteria regarding equol-producing ability.

In addition, we investigated the effects of ingestion of "equol + lactobionic acid" on lifestyle-related disease parameters such as vascular system, visceral fat area, and AGEs (advanced glycation end products) in the above subjects, and investigated the effects of equol production ability and intestinal bacteria. It is important to clarify the relationship with the background factors of equol in order to further build evidence on the action of equol.

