## 3. Method

- 1) Survey period: 12 weeks (August 2017-February 2018)
- 2) Test method: Epidemiological survey, clinical trial (randomized open trial)
- 3) Number of cases: 60 cases (30 women who take equol + lactobionic acid supplement, and 30 women who do not take the supplement)
- 4) Test food: "Equol + lactobionic acid" 3 tablets (10 mg) daily (marketed in December 2013)

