## 4. Measures

Before ingesting the supplement: Equol check (in urine), gut microbiota test (stool test), dietary habit assessment (BDHQ).

Before and after ingestion of supplement: height / weight / body composition, blood test (TG, HDL-C, LDL-C, T-CL, uric acid, HbA1C), baPWV, visceral fat CT test (fat scan), AGE measurement by AGE reader, and climacteric system assessments.

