## 5. Outcome evaluation

- 1) Primary Outcomes: blood test (TG, HDL-C, LDL-C, T-CL, uric acid, HbA1C), baPWV, visceral fat area
- 2) Key Secondary Outcomes: AGE, relationship between equol-producing ability, type of intestinal bacteria, and dietary habit assessment (BDHQ) from the test results, safety of supplement, climacteric symptoms

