## 7. Analysis

For the primary measures, perform chi-squared test and t test for comparison between groups and before and after the study period. For secondary outcomes, anonymized data are entered into the database and the correlation is analyzed. Drop out cases and missing values are not included in the analysis. Other questionnaire surveys will be conducted according to the evaluation criteria of each questionnaire. The visceral fat CT examination and baPWV measurement at the start of the test and at 12 weeks will be performed at the same site in order to eliminate measurement errors.

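### Diet is recorded at week 0 only in an open trial without placebo, so diet change that differs between the arms over 12 weeks would go largely undetected

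*Protocol*

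**What the plan says.** Section 3 of the Protocol describes the study as "Epidemiological survey, clinical trial (randomized open trial" with "60 cases (30 women who take equol + lactobionic acid supplement, and 30 women who do not take the supplement". There is no placebo.

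Section 4 places the dietary assessment at baseline: "Before ingesting the supplement: Equol check (in urine), gut microbiota test (stool test), dietary habit assessment (BDHQ". Section 6 agrees. The rows "Dietary questionnaire" and "Urine equol test" are each marked at week 0 and then only in the result-report column.

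Section 5 lists "Primary Outcomes: blood test (TG, HDL-C, LDL-C, T-CL, uric acid, HbA1C), baPWV, visceral fat area", and Section 6 schedules all of these at weeks 0 and 12. For these measures Section 7 will "perform chi-squared test and t test for comparison between groups and before and after the study period".

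Section 1 explains that equol is made by gut bacteria from a soy isoflavone, and that "the number of people who can produce equol in the body is as small as about 50% in Japan".

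Four other places bear on the point:

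- The selection criteria (Section 2) require a daily life diary for the 12 weeks. Its content is not stated, and it does not appear in Sections 4, 6 or 7.
- The exclusion criteria (Section 2) cover starting medicines or health foods during the test period.
- The Methods item of the Outline gives one timing line (start, monthly, end) for all investigations together, the eating-habit survey included.
- Section 11, item 3) requires the explanatory document to state the purpose and method of the study and the subject's own responsibilities. That document is not shown.

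**The concern.** Randomisation balances diet at week 0. It does not balance changes that follow from knowing one's assignment, and here every woman knows it. Consent comes a week before baseline and explains the purpose, so women in both arms know that equol is being tested. The protocol itself treats the outcomes as markers of lifestyle-related disease risk, and several of them (the lipids, uric acid, HbA1c, visceral fat) can be expected to respond to eating habits.

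Two differential changes are plausible, and they act in opposite directions. If women given the supplement also eat better, the difference between arms overstates what the supplement does. If control women who can produce equol eat more soy, they supply themselves with some of the compound under test and the difference shrinks. The stated objective is the effect of ingesting the supplement, so both bear on how a result may be attributed. No later analysis plan can use week-12 dietary data that were never collected.

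**Working it through.** **What the protocol fixes.** The dietary questionnaire and urine equol test are done at week 0 only, and the primary outcomes at weeks 0 and 12. There are 30 women per arm, and about 50% of people in Japan can produce equol. The protocol gives no alpha, power, effect size or SD, so it has no figure of its own to reproduce here.

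**Which comparisons are exposed.** A diet change of the same average size in both arms cancels in the between-arm difference. It does not cancel in a before-after test within an arm. Only differential change biases the between-arm test.

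**Dilution through soy in the control arm.** Let the supplement's effect be δ. Expected control producers: 0.5 × 30 = 15. Let a fraction f of them raise soy intake after consent, each gaining k × δ from her own equol. The control mean then moves by 0.5 × f × k × δ, and the observed contrast is

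δ × (1 − 0.5 × f × k).

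The documents give neither f nor k. Over a range of assumed values, the loss is:

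| | k = 0.25 | k = 0.5 | k = 1 |
|---|---|---|---|
| f = 1/3 (5 of 15 women) | 4.2% | 8.3% | 16.7% |
| f = 1 (all 15, ceiling) | 12.5% | 25% | 50% |

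These figures assume that no supplement-arm producer raises her soy intake. If producers in both arms change equally and the effects add, the loss is zero. Equol that women already produce from their usual diet at baseline is balanced by randomisation in expectation and is not counted.

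**What dilution would cost in power (illustration).** Assume a two-sided alpha of 0.05, a normal approximation and SD = 1. The standard error is √(2/30) = 0.258, and the difference detectable with 80% power is (1.960 + 0.842) × 0.258 = 0.72 SD. Reducing a true 0.72 SD by 10%, 20% or 50% lowers power to 71%, 61% or 29%.

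**Bias in the other direction (illustration).** Suppose the supplement has no effect, but diet improves more in the supplement arm by b SD. The chance of a nominally significant result per outcome is Φ(b/0.258 − 1.96) + Φ(−b/0.258 − 1.96). This gives 6.7% for b = 0.1, 12.1% for 0.2, 21.3% for 0.3 and 49.1% for 0.5, against a nominal 5%. The documents give no value for b.

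**What could reveal a change.** Weight and body composition, measured before and after, say something about energy balance but nothing about soy. The diary might hold dietary information, but the protocol does not say so and plans no use of it. The exclusion criterion covers health foods, which plausibly include equol or isoflavone products, but not ordinary soy foods. The Outline's timing line is general, and Sections 4 and 6 are specific in placing diet at baseline.

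**The case against.** The strongest defence is that the week-0 questionnaire serves its stated purpose. The protocol wants diet, gut bacteria and equol-producing ability related to one another, and a baseline measurement does that. Nothing promises a diet-adjusted effect, so a week-12 repeat is an added measurement and not the repair of an error. This stands, and it limits the weight of the point.

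It can also be said that the usual-diet instruction may exist. The explanatory document must cover the subject's responsibilities, which is a natural place for it. This stands too: one can say only that the protocol shown contains no such instruction.

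A further objection is that the root problem is open allocation, and that a self-report from unblinded women may itself be coloured by assignment. That is fair. A repeat questionnaire can reveal a differential change but cannot recover the undistorted effect.

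A reader might infer more than the documents support, in three ways:

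- That extra soy in the control arm could be mistaken for a supplement effect. It would hide or dilute one. Only differential improvement in the supplement arm could imitate benefit.
- That half the controls being potential producers means up to half the effect is lost. That needs every control producer to raise her soy intake, her own equol to work as well as the supplement, and no matching change in the other arm.
- That the trial has no means at all of noticing dietary change. Weight, body composition and possibly the diary give partial checks.

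**Conclusion.** The point holds as a cheap improvement of low to moderate severity. Sections 4 and 6 put the only defined dietary measurement at week 0, in an open trial without placebo whose primary outcomes, several of them diet-sensitive, are read at week 12. The protocol shown neither restrains ordinary diet and soy intake nor clearly records them during follow-up.

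The between-arm test is threatened only by differential change; the before-after tests are exposed to any change. Dilution through control-arm soy is bounded by about 0.5 × f × k: 4% to 17% if a third of control producers raise soy intake, and 12.5% to 50% as a ceiling if all do. It is smaller if supplement-arm women do the same. The possible overstatement in the other direction cannot be sized from the documents. The 50% producer share is the protocol's figure for Japan in general; f, k, b and alpha are assumptions.

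The randomised contrast still estimates the effect of being assigned the supplement under open conditions. What is weakened is attributing that contrast to ingestion of the supplement alone.

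**What to change.** 1. At week 0, give both arms the same instruction to keep their usual diet, soy intake and exercise, and state it in the protocol. If the explanatory document already contains it, refer to it.
2. Repeat the self-administered BDHQ at the existing week-12 visit in both arms, and add it to Sections 4 and 6.
3. Report the change in energy and soy intake by arm beside the primary results, as a descriptive check. Do not adjust the primary comparison for it, because it is measured after randomisation.
4. If intake changed differently between arms, qualify any attribution of the difference to the supplement.
5. Align the general timing line in the Outline with Sections 4 and 6, and state what the daily life diary records.

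The cost is one further questionnaire for 60 women at a visit already planned, its scoring, and one table. The downsides are some participant time and the possibility that unblinded women's answers are affected by knowing their assignment. Repeating the urine equol test in the control arm at week 12 would be a more direct check on equol exposure, at the price of an additional assay; it is optional.

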## 7. Analysis

For the primary measures, perform chi-squared test and t test for comparison between groups and before and after the study period. For secondary outcomes, anonymized data are entered into the database and the correlation is analyzed. Drop out cases and missing values are not included in the analysis. Other questionnaire surveys will be conducted according to the evaluation criteria of each questionnaire. The visceral fat CT examination and baPWV measurement at the start of the test and at 12 weeks will be performed at the same site in order to eliminate measurement errors.

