## **Outline of Research**

### **1. Objective**

To investigate the relationship between dietary status, type of intestinal bacteria, and equol-producing ability.

To examine the effects of ingestion of "equol + lactobionic acid" on various parameters of lifestyle-related disease risk such as arteriosclerosis and visceral fat area including the relationship with the above background factors.

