#### **2) Selection, exclusion, discontinuation criteria**

##### **① Selection criteria**

Those who meet all of the following selection criteria and have the ability to consent are eligible.

- Japanese healthy postmenopausal women over 50 years old
- Persons undergoing medical examination at Sendai General Clinic
- Persons who can undergo interviews or examinations at the start of the examination and every month at the Sendai General Clinic (8 minutes on foot from JR Sendai Station)
- Person who can take the recommended quantity of supplement and record daily life diary during the implementation period (12 weeks)

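### Section 7 puts before/after tests on the primary measures beside the between-group tests without saying which decides the supplement effect

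*Protocol*

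**What the plan says.** Protocol section 3 (Method) describes the design as "Epidemiological survey, clinical trial (randomized open trial") and sets the allocation at "60 cases (30 women who take equol + lactobionic acid supplement, and 30 women who do not take the supplement"). It gives the timing as "Survey period: 12 weeks (August 2017-February 2018").

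Section 5 lists "Primary Outcomes: blood test (TG, HDL-C, LDL-C, T-CL, uric acid, HbA1C), baPWV, visceral fat area". That is six blood tests plus two further measures, eight in all. The schedule in section 6 collects each of them at week 0 and at week 12.

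Section 7 (Analysis) then states: "For the primary measures, perform chi-squared test and t test for comparison between groups and before and after the study period". It does not say which of the two comparisons settles whether the supplement works, and it does not label the before/after comparison as descriptive. No other section of the protocol makes the randomised contrast decisive.

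**The concern.** The stated objective is the effect of taking the supplement. With a randomised concurrent control, the difference between arms answers that question, because anything that moves both arms equally cancels out. A before/after test has no such protection. It asks whether the mean change is zero, and the mean change includes whatever else shifted over the 12 weeks.

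Two sources of common shift are plausible from the protocol itself:

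- **Calendar drift.** Each woman's baseline and week-12 visits are 12 weeks apart within a window running from August to February, so diet, activity and season can differ between them.
- **Behaviour change.** The women join at a medical examination, know their allocation, attend monthly and are asked to keep a daily diary. Any of these can alter habits in either arm.

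The rule in section 7 that CT and baPWV be repeated at the same site limits measurement differences, but it removes neither source.

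If the two comparisons carry equal standing, a report could rest a claim on a significant before/after result in the supplement arm, or on significance there and not in the control arm. Neither is a test of the difference between arms.

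**Working it through.** The protocol gives no alpha, power, effect size or SD for this analysis, so there is no figure of its own to reproduce. The calculation below is an illustration.

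**Inputs**

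- n = 30 per arm (section 3).
- Eight primary measures (section 5).
- Two-sided alpha 0.05 (assumed).
- No supplement effect (the null case of interest).
- A common drift in both arms of d standard deviations of the individual change (assumed; the documents give no value, so a range is shown).
- Changes roughly normal, arms independent.

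**Step 1: before/after test in the supplement arm.** The paired t statistic follows a noncentral t distribution with 29 degrees of freedom and noncentrality d × √30. The two-sided critical value is 2.045. The probability of significance is p(d) = P(|T| > 2.045). For example, at d = 0.3 the noncentrality is 0.3 × 5.477 = 1.643 and p = 0.355.

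**Step 2: significant in the supplement arm, not in the control arm.** The arms are independent and share the same drift, so the probability is p × (1 − p). At d = 0.3 this is 0.355 × 0.645 = 0.229.

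**Step 3: between-arm t test on change.** The common drift cancels. Simulation with 40,000 replicates gave rejection rates of 0.048, 0.050 and 0.050 at d = 0, 0.3 and 0.5.

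| Drift d (SD of change) | Supplement-arm before/after test significant | Supplement significant, control not | Between-arm test of change |
|---|---|---|---|
| 0 | 0.05 | 0.05 | 0.05 (simulated) |
| 0.1 | 0.08 | 0.08 | 0.05 |
| 0.2 | 0.19 | 0.15 | 0.05 |
| 0.3 | 0.36 | 0.23 | 0.05 (simulated) |
| 0.4 | 0.56 | 0.25 | 0.05 |
| 0.5 | 0.75 | 0.19 | 0.05 (simulated) |

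The rows without simulation follow from the cancellation of d.

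**Step 4: bounds and direction.** The product p(1 − p) cannot exceed 0.25. It comes close to that ceiling at d = 0.36 (p = 0.479) and falls again at larger drift, because the control arm then tends to be significant too. The probabilities are two-sided. With drift in the favourable direction nearly all of the 0.23 at d = 0.3 would look like benefit. With unfavourable drift of the same size, a false benefit in the supplement arm only has a probability of about 0.0001.

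**Step 5: eight measures.** If the eight were independent with the same d (an assumption; lipids in particular are correlated), the chance of at least one significant supplement-arm before/after test would be 1 − (1 − p)^8. This gives 0.34 at d = 0 and 0.81 at d = 0.2. The 0.34 is ordinary multiplicity and would apply equally to eight between-arm tests. Only the rise above it is due to drift.

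**The case against.** The strongest reply is that the plan already contains the valid test. The between-group comparison is prescribed and is named first. Section 7 never says that a before/after result would support a conclusion, and an SAP, if one exists, could rank the two. This stands in part. A reader might infer that the plan discards the control arm or makes within-arm testing its primary analysis, but the text supports neither; the fault is that the two comparisons are unranked. A possible SAP does not remove it, because the protocol itself prescribes both tests for the primary measures and an SAP that followed it would carry both.

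A second reply is that the sentence could loosely mean a between-group comparison of before-to-after change. That is possible, but the wording more naturally names two comparisons, and a before/after test pooled over both arms would be no better. If change between arms was meant, the sentence still needs to say so. This reading also warns against simply striking the before/after phrase, since it is the only wording in section 7 that brings baseline into the primary analysis.

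Third, some mechanisms are weak here. Regression to the mean is a tempting addition, but the selection criteria ask for "Japanese healthy postmenopausal women over 50 years old" and set no entry threshold on any primary measure, so little shift in an arm's mean is expected from it. Nor does every woman span summer to winter: each is followed for 12 weeks inside the longer window. Both limits stand. Calendar and behaviour drift carry the point.

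Finally, the size of the drift is not in the documents, and its direction could differ between measures. That also stands, which is why the table starts at zero.

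**Conclusion.** The point holds as a lack of ranking. Section 7 prescribes before/after significance tests on the primary measures beside the randomised comparison and leaves open which one decides the supplement effect. Followed as written, it allows drift common to both arms to be read as an effect.

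How much this matters depends on a drift that the documents do not quantify. With none, the supplement-arm test errs at its nominal 0.05. At 0.2 SD of change the rate is 0.19 and at 0.5 SD it is 0.75, while the between-arm test of change stays at about 0.05. The one-arm-only pattern never exceeds 0.25 and misleads towards benefit only when drift is favourable. These figures describe false conclusions only if conclusions are drawn from those tests, which the protocol permits but does not state. The logical fault does not depend on the size of the drift: significance in one arm and not in the other is not a test of their difference.

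Severity: should be fixed. The valid comparison is already planned, and what is missing is the statement that it alone decides.

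**What to change.** Rewrite the sentence in section 7 to say three things:

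1. The supplement effect on each primary measure is judged only on the between-arm difference in 12-week change.
2. The preferred analysis is ANCOVA of the week-12 value on arm, with the week-0 value as covariate.
3. Changes within each arm are reported descriptively, as means with 95% confidence intervals, and no conclusion on efficacy is drawn from them.

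The rewrite should replace the before/after phrase with this explicit use of baseline, not merely delete it; otherwise it is unclear whether change, a baseline-adjusted value or the raw week-12 value is compared.

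The cost is a short edit. Both values are already collected under the section 6 schedule, so no extra visits, measurements or participants are needed. The one thing given up is that within-arm p-values can no longer support a claim.

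### Section 7 names a chi-squared test beside a t test for eight primary outcomes that are all continuous, without saying which test serves which comparison

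*Protocol*

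**What the plan says.** Section 5 (Outcome evaluation) lists the primary outcomes: "Primary Outcomes: blood test (TG, HDL-C, LDL-C, T-CL, uric acid, HbA1C), baPWV, visceral fat area". That is six blood values, pulse wave velocity and a fat area: eight measurements, all on a continuous scale. The protocol defines no responder, normal/abnormal class or threshold for any of them.

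Section 7 (Analysis) then states: "For the primary measures, perform chi-squared test and t test for comparison between groups and before and after the study period". Two tests and two kinds of comparison are named in one sentence, and neither test is assigned to a comparison or to an outcome.

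The before/after comparison concerns the same women. Section 4 (Measures) lists "blood test (TG, HDL-C, LDL-C, T-CL, uric acid, HbA1C), baPWV, visceral fat CT test (fat scan" among the items taken both before and after supplementation. The schedule in section 6 places the blood test, baPWV and visceral fat scan at weeks 0 and 12, and section 7 adds: "The visceral fat CT examination and baPWV measurement at the start of the test and at 12 weeks will be performed at the same site".

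The design in section 3 (Method) is "Epidemiological survey, clinical trial (randomized open trial" with "60 cases (30 women who take equol + lactobionic acid supplement, and 30 women who do not take the supplement".

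**The concern.** A chi-squared test compares counts in classes. None of the named primary outcomes comes in classes, so the test cannot be run as the protocol stands. Someone must first cut each outcome, and the cut discards information that a trial of 60 women can ill afford to lose.

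The sentence also leaves open what decides each outcome. Read literally, both tests apply to both comparisons. Each outcome then gets two p-values for the same between-arm question, 8 × 2 = 16 in all, and nothing says which one counts. On that reading chi-squared is also applied to week 0 and week 12 classes from the same women, although the ordinary test assumes independent observations.

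**Working it through.** **No figure to reproduce.** The protocol states no alpha, power, effect size, SD or within-woman correlation, and gives no derivation for 60 women. What follows is illustration under stated assumptions: two-sided alpha 0.05, normal outcomes, 30 women per arm (section 3).

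**1. Information kept by a median split.** The asymptotic efficiency relative to the t test is 2/π = 0.637, about 64%. This is the best case; an off-centre cut keeps less.

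**2. Between-arm power at 30 per arm.** Let d be the true difference in SD units.
- t test (normal approximation): Φ(d/√(2/30) − 1.96). At d = 0.5: 0.5/0.2582 = 1.937, and Φ(1.937 − 1.960) = 0.49.
- Chi-squared, cut midway between the arm means: the proportions are Φ(0.25) = 0.599 and 0.401, a difference of 0.197. The standard error is √(2 × 0.25/30) = 0.1291 under the null and √(2 × 0.599 × 0.401/30) = 0.1266 under the alternative. Power = Φ((0.197 − 1.96 × 0.1291)/0.1266) = Φ(−0.44) = 0.33.

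| d | t test | chi-squared, midpoint cut |
|---|---|---|
| 0.3 | 21% | 15% |
| 0.5 | 49% | 33% |
| 0.8 | 87% | 68% |

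If the cut leaves 20% of one arm above it and the other arm lies 0.5 SD lower, chi-squared power falls further, to 22%.

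For 80% power at d = 0.5, the t test needs 63 women per arm and the midpoint-cut chi-squared needs 100. The ratio 63/100 = 0.63 agrees with step 1.

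**3. Chi-squared on before/after classes in the same women.** Let φ be the correlation between a woman's before class and her after class. The true variance of the difference in proportions is (1 − φ) times the variance that the unpaired test assumes. The true size of a nominal 5% test is therefore 2 × (1 − Φ(1.96/√(1 − φ))).
- φ = 0.4: 1.96/√0.6 = 2.530, size 0.0114, about 1.1%.
- φ = 0.6: 1.96/√0.4 = 3.099, size 0.0019, about 0.2%.

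φ is not the correlation of the measurements themselves. For a median split of bivariate normal values, φ = (2/π) arcsin ρ, so ρ = sin(πφ/2). This gives ρ = 0.59 for φ = 0.4 and ρ = 0.81 for φ = 0.6.

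**4. Check by simulation.** With 30 pairs, 40,000 runs and a cut midway between the two means, the size of the unpaired chi-squared test was 5.0% at ρ = 0, 1.8% at 0.5, 0.7% at 0.7 and 0.05% at 0.9. This is consistent with step 3. For a true change of 0.5 SD and ρ = 0.7, power was 29% for unpaired chi-squared, 52% for McNemar's test and 93% for the paired t test.

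**5. Readings of the sentence.**
- Both tests for both comparisons (literal): steps 2 and 3 both apply to the chi-squared results, alongside valid t tests.
- Chi-squared between groups, t test before/after (in the order named): step 3 falls away, but the randomised comparison rests on dichotomised data alone, so step 2 applies in full.
- Each test where the data type fits: no primary measure is categorical, so chi-squared has nothing to apply to.

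On none of these readings does the reference to chi-squared fit the primary measures.

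**The case against.** The strongest reply is that the same sentence also prescribes a t test, which uses the full continuous data. This stands. A reader might infer from the 64% figure that the whole primary analysis is degraded and that 60 women act like about 38 (60 × 0.637 = 38.2). The protocol does not support that: the loss applies only to conclusions resting on a dichotomised chi-squared test.

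The sentence is also ambiguous, and the pairing problem exists only if chi-squared is used before versus after. This stands too, so that part of the point is conditional. The alternative reading is no rescue, however, because it moves the between-arm comparison onto chi-squared.

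A reader might take ignored pairing to mean extra false positives. With positive within-woman correlation the opposite holds: the test is conservative and misses real changes.

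Finally, cut-points and the paired test for classes are details that a statistical analysis plan may supply, and only the protocol was available here. Their absence is therefore not held against it, and nothing shows that cuts would be chosen after seeing the data. What remains is what the protocol itself fixes: a test for categorical data, assigned to measures that are all continuous. An analysis plan could carry that out only by inventing classes, or drop it only by departing from the protocol.

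**Conclusion.** The point holds in a limited form. Section 7 assigns a chi-squared test to eight outcomes that are all continuous, and does not say which test answers which question. This needs correcting on any reading, but it does not invalidate the trial, since a suitable test stands in the same sentence.

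If conclusions were drawn from chi-squared between arms, the cost would be 6 to 21 percentage points of power for differences of 0.3 to 0.8 SD, the largest near 0.72 SD (80% against 59%). If chi-squared were used before versus after, its true size would be about 1% or less for measurement correlations of about 0.6 and above. These sizes rest on normal outcomes, alpha 0.05, complete data on 30 women per arm and assumed correlations. Section 7 also says "Drop out cases and missing values are not included in the analysis", so the number analysed may be smaller and power lower for both tests.

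**What to change.** Rewrite the first sentence of section 7:
- Delete chi-squared for the primary measures.
- Name one between-arm analysis of each outcome on its continuous scale as primary: a t test on the change from week 0 to week 12, or the week 12 value adjusted for baseline.
- State that within-arm before/after t tests are paired and supportive.
- Keep chi-squared or Fisher's exact test for truly categorical data, such as the occurrence of an adverse event by arm.
- If a normal/abnormal classification is wanted, fix its limits in advance, report it as supportive, and use McNemar's test for any paired comparison of the classes.

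The cost is a short rewording of section 7. No additional women, visits or measurements are needed.
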